### Outcomes

Following written informed consent and full eligibility assessment, all eligible patients will be assessed on all outcomes before randomisation (‘baseline’), after the 8-week intervention period (‘post-intervention’), and after a 6-month and 12-month follow-up periods (‘follow-up’) by blinded assessors (see Fig. 1). Secondary outcomes and process measures using the Experience Sampling Method (ESM) will be assessed at baseline, post-intervention, and 6-month follow-up.

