### Statistical analysis

The investigators will access the final trial dataset to test the primary hypothesis of a reduction in distress associated with psychotic experiences measured with the CAARMS using a linear regression model with distress at all three time points (i.e. post-intervention, 6-month and 12-month follow-ups) as the dependent variable and distress at baseline, condition (ACT-DL + TAU vs. TAU), time (as a three-level factor), centre (as a five-level factor), the baseline × time interaction, and the condition × time interaction as independent variables, according to the intention-to-treat principle. Within-subject clustering of repeated measures will be taken into account by allowing residuals within subjects to be correlated with a completely unstructured variance-covariance matrix.

The model will be fitted using restricted maximum likelihood estimation using Stata 15 [85]. This will allow for the use of all available data under the assumption that data is missing at random and if all variables associated with missing values are included in the model [86, 87]. Hence, bias due to attrition over time, due to difference between groups, or as a function of baseline distress is already mitigated by the model. Potential bias due to missing outcomes will be assessed in descriptive analyses of baseline characteristics stratified by missing data for the primary outcome and condition as follows: (a) experimental condition with no missing primary outcome at post-intervention time point, (b) experimental condition with missing primary outcome at post-intervention time point, (c) control condition with no missing primary outcome at post-intervention time point, and (d) control condition with missing primary outcome at post-intervention time point [88, 89].

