The main effect of condition will be tested via an omnibus test of no difference between the two conditions at all three time points (Wald-type test with df = 3 and alpha = .05). Should the omnibus test be statistically significant, then the three time-specific contrasts will be examined to determine at which time points significant differences are present (each tested at alpha = .05). Secondary hypotheses and analyses of process measures to assess putative mechanisms of change will be tested following the same steps. Given that block randomisation will be carried out in blocks of six participants, with stratification for centre and group, all analyses will include centre and group as covariate, even though there is little reason to expect noteworthy clustering of outcomes by centre.

In addition, multilevel mediation analysis will be used to test indirect effects of condition on primary outcomes (distress associated with psychotic experiences) and secondary outcomes (psychotic experiences, psychopathology, social functioning) via pathways through putative mechanisms of change (psychological flexibility, stress sensitivity, reward experience). Multilevel mediation models will be fitted in MPlus, Version 7 [90], to control for within-subject clustering of multiple time points [91, 92], using the MLR estimator, which allows for the use of all available data under the assumption that data is missing at random (if all variables associated with missing values are included in the model). In a two-level model, multiple time points (level 1) will be treated as nested within subjects (level 2). The total effect of condition (level 2) on primary/secondary outcomes (level 1) will be apportioned into direct and indirect (or, synonymously, mediating) effects through putative mechanisms of change (level 1) using the product of coefficients strategy. This strategy quantifies the point estimate of the indirect effect as the product of the coefficient of independent variable on mediator variable (path a) and the coefficient of mediator variable on dependent variable (path b). We will use statistical software by Selig and Preacher [93] for computing Monte Carlo confidence intervals and assessing the statistical significance of indirect effects, given their advantages over rival methods in the context of multilevel mediation models [93, 94].

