For analysis involving ESM variables, multiple ESM observations (level 1) will be treated as nested within time points (baseline, post-intervention, 6-month follow-ups) (level 2) and time points as nested within subjects (level 3). Consistent with established credibility criteria [48], we will further test the effects of ACT-DL in UHR compared with FEP individuals in a-priori planned subgroup analyses. For subgroup analyses comparing UHR and FEP, data on the group variable (UHR, FEP) will be measured prior to randomisation (to address the criterion that the subgroup characteristic is measured at baseline) to investigate whether there is a difference in the reduction in distress associated with psychotic experiences measured with the CAARMS of large effect size between UHR and FEP participants (to address the criterion that the expected difference/effect size is specified a priori) given that only a large effect size would be relevant for implementation of ACT-DL in routine care. It will further be examined whether this effect is (a) consistent across (primary and secondary) outcomes and (b) supported by indirect evidence on putative mechanisms of change (psychological flexibility, stress sensitivity, reward experience). In more exploratory sensitivity analyses, we will compare ACT-DL + TAU, CBTp + TAU and TAU only to investigate whether the reduction in distress associated with psychotic experiences measured with the CAARMS will be greater for CBTp + TAU than TAU only as well as for ACT-DL than CBTp.

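### ESM mediation models, read literally, include the pre-randomisation visit under a single condition effect, which would dilute path a and the total effect

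*Protocol article*

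**What the plan says.** All statements are in the protocol article.

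- **ESM schedule (Outcomes).** "Secondary outcomes and process measures using the Experience Sampling Method (ESM) will be assessed at baseline, post-intervention, and 6-month follow-up". Baseline is before randomisation: patients "will be assessed on all outcomes before randomisation (‘baseline"’). ESM therefore has three visits, two of them after randomisation.
- **ESM analyses (Statistical analysis).** Momentary observations "will be treated as nested within time points (baseline, post-intervention, 6-month follow-ups) (level 2) and time points as nested within subjects (level 3"). The sentence covers every analysis that involves ESM variables.
- **Mediation (Statistical analysis).** The data structure is given as follows: "In a two-level model, multiple time points (level 1) will be treated as nested within subjects (level 2"). Condition enters at the subject level, and its effect is then split: "The total effect of condition (level 2) on primary/secondary outcomes (level 1) will be apportioned into direct and indirect" components. Path a is described as one coefficient of condition on the mediator. No condition-by-time term, baseline covariate or list of visits is given.
- **Mediators (Process measures and Statistical analysis).** Stress sensitivity and reward experience, two of the three named mechanisms, are operationalised through ESM. Psychological flexibility is measured partly by ESM.
- **Primary model (Statistical analysis).** The three follow-up visits are the outcomes, and the predictors include "distress at baseline, condition (ACT-DL + TAU vs. TAU), time (as a three-level factor"), plus baseline-by-time and condition-by-time interactions. Baseline is a covariate. Secondary and process measures are to be tested in the same way.

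**The concern.** The second aim asks whether ACT-DL changes the mechanisms and secondary outcomes after treatment. The primary model fits that kind of question, because baseline is a predictor and only post-randomisation visits are outcomes. The ESM sentence instead lists baseline alongside the two later visits, and the mediation text gives condition one coefficient per path. Together they describe a model in which that coefficient is an average over visits, one of which cannot carry an effect. Chance baseline imbalance would also enter the coefficient directly rather than being adjusted for.

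At stake is the mechanism evidence. The Discussion relies on it when it says that findings on putative mechanisms will help to assess causality under real-world conditions. A diluted path a could lead to a real mechanism being reported as unsupported, and a larger sample would not remove the bias.

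**Working it through.** **Inputs from the protocol (Sample size):** 75 per arm at baseline; 31% attrition, which is 75 × 0.31 = 23.25, taken as 23 per arm; 52 per arm remaining (104 in total); d = 0.5; two-sided alpha 0.05.

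**Assumptions:** within-person correlation r between visits is not given, so a range is shown. The effect is d at both post-randomisation ESM visits. The mediator is treated as one value per visit with unit variance. Those lost contribute baseline only.

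**1. The plan's own figure.** The protocol gives no power for ESM or mediation. Its 0.92 for the primary 3-df test is approximately reproduced if d = 0.5 holds at all three follow-ups. The noncentrality is (52/2) × 0.25 × 3/[(1 − r²) + 2(r − r²)]. At r = 0.5 this is 6.5 × 2.4 = 15.6, power 0.928. At r = 0.2, 0.3 and 0.4 power is 0.921, 0.910 and 0.913. The inputs are therefore usable.

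**2. Dilution, complete data.** With time as a factor, one condition coefficient and exchangeable correlation, the three visits get equal weight:

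(0 + d + d)/3 = 0.667 d.

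This value does not depend on r. Under an autoregressive pattern with adjacent correlation 0.5 or 0.7 it is 0.60 d or 0.57 d.

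**3. Dilution with 31% attrition.** Per arm, 52 people have all three visits and 23 have baseline only. Each follow-up visit gets weight 52/(1 + 2r), and baseline gets 52/(1 + 2r) + 23. Hence

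coefficient/d = 104 / [156 + 23(1 + 2r)].

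| r | 0 | 0.3 | 0.5 | 0.7 | 0.9 |
|---|---|---|---|---|---|
| coefficient/d | 0.58 | 0.54 | 0.52 | 0.49 | 0.47 |

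For example, at r = 0.5: 104/(156 + 46) = 0.515. Baseline supplies 150 of the 150 + 104 + 104 = 358 person-visits, or 42%. The autoregressive pattern gives 0.47 d (adjacent correlation 0.5) and 0.43 d (0.7).

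**4. Illustrative power for path a, d = 0.5.**

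- *Baseline as an occasion, complete data, 52 per arm:* SE = √[(2/52)(1 + 2r)/3]. At r = 0.5 this is 0.160; z = 0.333/0.160 = 2.08; power 0.55.
- *Baseline as an occasion, with attrition:* SE = √{2/[156/(1 + 2r) + 23]}. At r = 0.5 this is √(2/101) = 0.141; z = 0.5 × 0.515/0.141 = 1.83; power 0.45.
- *Two follow-ups, baseline as covariate, 52 per arm:* SE = √{(2/52)[(1 + r)/2 − r²]}. At r = 0.5 this is 0.139; z = 3.61; power 0.95.

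| r | occasion, complete | occasion, attrition | covariate |
|---|---|---|---|
| 0.3 | 0.64 | 0.55 | 0.93 |
| 0.5 | 0.55 | 0.45 | 0.95 |
| 0.7 | 0.48 | 0.37 | 0.99 |

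**5. ESM efficacy tests.** A model with condition-by-time terms estimates each visit's effect separately, so nothing is diluted. Two post-randomisation visits give a 2-df test. Power at r = 0.3, 0.5 and 0.7 is 0.87, 0.91 and 0.98. Referring the same noncentrality to 3 df would give 0.83, 0.87 and 0.96, so the degrees of freedom matter little here.

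**The case against.** The strongest reply is that the ESM sentence describes only a data hierarchy. Baseline observations sit in that hierarchy under any sound analysis, including one that derives a baseline covariate or constrains the baseline effect to zero. The sentence does not call baseline an outcome or mediator row, and the mediation paragraph names no visits. In the preceding text, the three time points are the post-randomisation ones. A journal article may also leave time coding to the full protocol or statistical code, which the authors offer on request. Finally, the mediation model has two levels and the ESM hierarchy three, and stress sensitivity and reward experience are within-person slopes rather than one value per visit, so the calculation simplifies them.

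Much of this stands. The link is an inference, and the figures are illustrative. It does not clear the text, however. The only list of time points given for ESM analyses includes baseline, and nothing in the mediation description removes it or separates its effect. If a covariate was intended, the wording points the other way.

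A reader might go further in four ways that the document does not support:

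- **A fixed loss of one third.** It requires complete data and exchangeable correlation.
- **A loss of one quarter for non-ESM mediators.** Nothing places baseline among the occasions of those models.
- **A baseline contrast within the ESM efficacy tests.** Those tests follow the primary approach, with baseline as covariate and condition-by-time terms. The 3 df are stated for the primary test.
- **An indirect effect reduced by the same factor.** That holds only if path b is unchanged.

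**Conclusion.** The point holds conditionally and concerns mediation with ESM variables. If those models are fitted as the two descriptions read together, path a and the total effect are biased towards zero: to 2/3 of the true effect with complete data and exchangeable correlation, and to 0.47 to 0.58 of it under the protocol's attrition for r from 0.9 down to 0. These factors assume equal effects at both follow-up visits, a mediator with one value per visit, and a correlation that the protocol does not give. At d = 0.5 and r = 0.5 with attrition, power for path a would be about 0.45, against 0.95 with baseline as a covariate. The primary test is untouched. The ESM efficacy tests are largely protected and need only their degrees of freedom stated. The wording should be corrected before analysis, because two of the three named mechanisms depend on it.

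**What to change.** In the Statistical analysis section, state one of the following for ESM efficacy and mediation models:

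1. ESM outcome and mediator occasions are post-intervention and 6-month follow-up only. The baseline ESM value (person mean, or baseline reactivity for stress sensitivity and reward experience) is a subject-level covariate with its time interaction, as in the primary model.
2. Baseline remains an occasion, the condition effect there is constrained to zero, and path a and the total effect are defined from the post-randomisation condition terms.

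In the mediation paragraph, name the visits that each ESM mediation model uses. State the omnibus test for ESM outcomes as 2 df.

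The cost is wording and a small change to model code; no new data or participants are needed. Option 1 needs an approach for participants without usable baseline ESM data, which option 2 avoids.

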### Interventions

#### Control condition: treatment as usual (TAU)

Participants allocated to the treatment as usual (TAU) control condition will continue to receive all the treatment they received prior to the start of the study. This will include good standard care delivered according to local and national service guidelines and protocols by their general practitioner, psychiatrist and other members of the mental health care team. Standard mental health care will include CBTp at some sites, which will be assessed together with other service contacts using a service-use checklist to monitor variation in the delivery of mental health services and allow for planned subgroup analysis.

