#### Experimental condition: ACT-DL + TAU

Participants allocated to the experimental condition will receive ACT-DL with trained clinicians within an 8-week period in addition to TAU, which will consist of all the treatment that they received prior to the start of the study and include all the input from their general practitioner, psychiatrist, and other members of the mental health care team that they would receive if they did not participate in the study, with the exception of manualised CBTp. The intervention can be discontinued by participants at any time upon request without any negative consequences.

The manualised ACT-DL intervention consists of eight ACT training sessions (including one session for psychoeducation) administered face-to-face by a trained clinician (i.e. psychologists having received a 5-day training in ACT-DL and receiving fortnightly supervision sessions for the purposes of the trial), each for around 45–60 min, and an ACT-based EMI, which participants will receive following randomisation to the experimental condition [46], over an 8-week intervention period. The latter will be administered through a smartphone-based app (i.e. the PsyMate™ app) to allow participants to apply the skills that they have been trained into their daily lives [28–30]. The first six face-to-face ACT sessions are based on a modified version of ACT for people with psychosis [35, 43, 44, 51] and aim to enhance participants’ psychological flexibility by training them in six core components: creative hopelessness, acceptance, cognitive defusion, self as context and contact with the present moment, values, and committed action [46, 52]. In the last session, all six components will be integrated and reviewed.

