### Randomisation and blinding

Participants will be randomised at a 50:50 ratio to the experimental or control condition at the level of the individual participant by an independent researcher through a computer-generated sequence following informed consent, full eligibility assessment, and assessment of all outcome measures. Block randomisation will be carried out in blocks of six participants, with stratification for the five centres (Amsterdam, The Hague, Maastricht/Eindhoven, Flemish-Brabant, East/West Flanders) and two groups of UHR and FEP (expecting a 50:50 ratio of UHR and FEP to be included in the sample). The researchers will be blind to the allocation of participants to the experimental and control group of the study. There will be a contact person for any questions regarding the procedure that is not involved in any testing to allow researchers to be blind towards the allocation of participants when assessing outcomes. Any breaks in blindness will be documented and another researcher will be allocated to complete the next set of assessments where possible.

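### The exploratory comparison of ACT-DL, CBTp and TAU is not randomised: it sets the whole experimental arm against parts of the control arm defined by care received, and is open to confounding in an unknown direction

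*Protocol article*

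**What the plan says.** All references are to the protocol article.

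- **Randomisation and blinding.** There are two conditions: "Participants will be randomised at a 50:50 ratio to the experimental or control condition at the level of the individual participant". Allocation is in blocks, "with stratification for the five centres (Amsterdam, The Hague, Maastricht/Eindhoven, Flemish-Brabant, East/West Flanders) and two groups of UHR and FEP". Neither receipt nor availability of CBTp is a stratum.
- **Control condition.** "Standard mental health care will include CBTp at some sites, which will be assessed together with other service contacts using a service-use checklist". The stated purpose of the checklist is "to monitor variation in the delivery of mental health services and allow for planned subgroup analysis".
- **Abstract, Methods/design.** Access to routine care and, where applicable, CBTp lasts for the whole study period, so CBTp may begin after randomisation.
- **Experimental condition.** Participants keep the usual care "that they would receive if they did not participate in the study, with the exception of manualised CBTp".
- **Statistical analysis.** Under the label of more exploratory sensitivity analyses, "we will compare ACT-DL + TAU, CBTp + TAU and TAU only". The question is whether the reduction in distress "will be greater for CBTp + TAU than TAU only as well as for ACT-DL than CBTp". The same section says that every analysis carries centre and group as covariates.

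**The concern.** The CBTp + TAU group can come only from the control arm, because manualised CBTp is excluded from the other. The ACT-DL group is a complete randomised arm and so includes people who would never have received CBTp. The CBTp group excludes such people. The two groups can differ in prognosis before any treatment effect, and randomisation does not protect the contrast. CBTp + TAU against TAU only lies wholly within the control arm and is observational throughout.

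The section sets a better standard a few lines earlier. For UHR against FEP it requires the subgroup variable to be measured before randomisation. It sets no such requirement for CBTp status.

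At stake is the reading of a secondary result. A difference between ACT-DL and an active therapy could be created, hidden or reversed by who was given CBTp and where.

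**Working it through.** **The plan's own figures.** Attrition: 75 × 0.31 = 23.25, so about 23 lost and 52 analysed per arm, 104 in all, as stated. The stated power of 0.92 (d = 0.5, omnibus test on 3 df) is reproduced with 52 per arm, the effect present at all three time points, adjustment for baseline and an assumed correlation of 0.5 between measurements: 0.928 (chi-square) or 0.917 (F). That figure belongs to the randomised comparison. The article gives no sample size or power for the three-way comparison.

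**Size of the possible error.** Two inputs are needed and neither is in the article, so both are assumed:

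- q, the share of controls who receive CBTp;
- g, the difference in prognosis, in SD, between controls who receive CBTp and other controls, left after adjustment.

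Suppose no treatment differs from any other. Take the mean of people who would not receive CBTp as 0 and of those who would as g. Randomisation gives both arms the same mix, so:

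- whole ACT-DL arm: q × g
- CBTp + TAU group: g
- TAU-only group: 0

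The spurious differences are then:

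- CBTp against ACT-DL: g − q × g = (1 − q) × g
- CBTp against TAU only: g
- ACT-DL against TAU only: q × g

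Check on the whole control arm: q × g + (1 − q) × 0 = q × g, the same as the ACT-DL arm. The randomised comparison is free of this error, and only the split creates it.

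| q | g | error, ACT-DL v CBTp: (1 − q) × g |
|---|---|---|
| 1/3 | 0.3 | 0.20 |
| 0.3 | 0.3 | 0.21 |
| 0.3 | 0.5 | 0.35 |
| 0.1 | 0.5 | 0.45 |
| 0.7 | 0.2 | 0.06 |

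A simulation of 20,000 trials at q = 0.3 and g = 0.3 gave 0.208, against 0.21 by formula.

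**Effect on the test.** At q = 0.3 there are 52 × 0.3 = 15.6 CBTp users. For one time point without adjustment, the standard error is √(1/52 + 1/15.6) = 0.289 SD. A nominal 5% test of a true null then rejects about 11% of the time at g = 0.3 and 23% at g = 0.5.

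**Precision.** With 17 CBTp users (about a third of 52) and an assumed correlation of 0.5 with baseline, the 95% half-width is 1.96 × √((1/52 + 1/17) × 0.75) = 0.47 SD. It is 0.59 with 10 users and 0.41 with 26. Even without confounding, the contrast would be imprecise.

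**What the stated adjustment removes.** Adjustment for centre and group handles differences between the five centres. But CBTp varies by site, and the Participants section shows that centres pool sites: Flemish-Brabant alone lists four. Differences between sites within a centre, and the indication for CBTp within a site, remain. The Other measures section lists potential confounders, but the article ties none of them to this comparison.

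**The case against.** The strongest reply is that the analysis is called exploratory, that none of the four study aims includes ACT-DL against CBTp, and that the Discussion claims no superiority over CBTp. All of that is true, and it limits the importance of the point. It does not answer it: exploratory signals tentativeness and does not tell a reader that the contrast is non-randomised, while the questions are worded in a direction.

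A reader might also infer more than the article supports:

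- *That controls select CBTp themselves.* The article names site provision and applicability and describes no choice by participants. Confounding by indication is a risk, not a documented fact.
- *That the result will be biased.* The error is zero if g = 0 after adjustment, and its sign is unknown. Adjustment for centre and group is planned, and the primary model also includes baseline distress.
- *That the split is by treatment started after randomisation.* The article does not say when CBTp status is fixed. Controls continue their earlier treatment, so classification at baseline is possible. Access throughout the study makes later receipt possible too. Fixing CBTp status at baseline in controls alone would still leave the undivided ACT-DL arm on the other side.
- *That calling it a planned subgroup analysis in one place and an exploratory one in another is a contradiction.* The control-condition text does not name the three-way comparison, and an analysis can be both planned and exploratory.

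The replacement proposed below also answers a somewhat different question from the one the plan asks. That objection stands, and its cost is given with the fix.

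**Conclusion.** The point holds in a limited form. The three-way comparison is non-randomised, and the article does not say so. ACT-DL against CBTp and CBTp against TAU only are open to confounding by site and indication, in an unknown direction, and the stated covariates deal with only part of it.

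On assumed inputs, the error in ACT-DL against CBTp is about 0.20 SD for q = 1/3 and g = 0.3, which is 0.20 / 0.5 = 40% of the design effect. It runs from 0.06 to 0.45 SD for q = 0.1 to 0.7 and g = 0.2 to 0.5. A figure of 0.3 SD in the central case would be right only if CBTp users differed by 0.3 SD from the arm as a whole, and not from the other controls. These figures illustrate scale; they do not predict a result.

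The primary intention-to-treat comparison of ACT-DL + TAU with TAU is not affected.

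**What to change.** Make the CBTp question a randomised one. Compare ACT-DL + TAU with TAU within strata fixed before randomisation and defined alike in both arms: whether the site offers CBTp, or CBTp being received at baseline if this is recorded in both arms. Test it as condition × stratum × time in the primary model and report it as exploratory. At sites that offer CBTp, this keeps a randomised contrast with care that includes CBTp.

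If the three-group comparison is kept, label it observational, state when CBTp status is fixed, adjust for baseline distress and the confounders listed under Other measures as well as centre and group, and draw no conclusion that ACT-DL exceeds CBTp or that CBTp exceeds TAU.

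**Cost.** Analysis wording, plus a record of which sites offered CBTp. No change to recruitment or assessments is needed for the site-level version. The interaction will have low power: the plan's own UHR/FEP interaction, with an expected even split, has 0.75 for d = 0.8, and an uneven CBTp split would do worse. It also gives no direct estimate of ACT-DL against CBTp, which this design cannot supply free of confounding.
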